### Informed Consent and Participant Privacy

Our consent and privacy processes closely follow the consent protocols established by Karra and Canning [40]. The process of obtaining consent was consistent for all potential participants: women and eligible husbands. Written consent to participate was obtained from all the participants before administering the surveys. Once participants agreed to join the study, a copy of the consent form script was read to them, and they were given opportunities to ask questions and express concerns. Surveyors checked for comprehension throughout the consent process, which took 5-10 minutes on average. Multimedia Appendix 1 presents the consent documents and details of the consent process. After completing the consent script, potential participants were asked if they would like to participate. If the participant wished to take further time to reflect, then the surveyor and the participant would determine the time and method of reconnecting. If the potential participant agreed to participate in the study, then consent was obtained and documented by obtaining the signatures of both the participant and the study staff member who provided consent. Upon providing consent, the surveyor would then conduct the survey.

For follow-up surveys, written consent to participate was obtained from women who were followed up either at home or at the clinic, and verbal consent to participate was obtained over the phone from participants who were originally recruited at baseline but who did not visit the clinic over the intervention period. Respondents who had previously indicated that they were no longer interested in participating in the study were not contacted. All survey responses were collected on Android (Google LLC)-based tablets, and data were securely transferred to the CommCare-supported server daily.

Throughout the consent process, each participant was informed that even if she decides to participate and sign the consent form, she could decide at any time to end her participation. If the prospective study participant was not literate, then a witness who did not work for the study signed the consent form. In the absence of witnesses, the participant could confirm their consent by placing a thumbprint on their consent form, and a photo of the thumbprint was taken as a record of consent. Moreover, participants were encouraged to contact the researchers with further questions at any time during the study. Consent was obtained before any surveys were conducted, and all participants were informed that their participation was completely voluntary.

All recruitment scripts, consent forms, and survey instruments were translated by a certified translator from English into Chichewa and were back-translated into English by a second certified translator to ensure accuracy.

When presented with the intervention, women were offered each intervention component (counseling and family planning package) by an interventionist from the study team. Women were informed that they could take up and stop any or all components of the intervention at any time. Counselors asked for a woman’s consent to participate before each counseling session.

All surveys and administration of the intervention were conducted in a private room. To maintain a respondent’s privacy during an attempt to reach her by phone, the field enumerator conducting the call left no indication of the reason for the phone attempt (eg, voicemail and text message) on the respondent’s phone should there be no response to a call. To ensure that the respondent’s participation remains private, the field enumerator only continued with the phone call once she received assurance from the woman that she was able to speak on the phone without being overheard or interrupted. Any disruption or interruption during the phone call resulted in postponement or termination of the call.

### Randomization

Following the baseline survey, women who consented to participate were randomized into 1 of the following 4 experimental arms:

A control group (T0), in which a woman received a private counseling session on the full range of 13 contraceptive methods following a standard counseling process (n=100).An intervention group (T1), in which a woman was encouraged (but not compelled) to invite her husband to a joint counseling session. A woman (and her husband if she chose to invite him) then received a private counseling session on a full range of 13 contraceptive methods (n=200).An intervention group (T2), in which a woman received a private counseling session on 5 targeted contraceptive methods based on her baseline preferences for family planning (n=200).An intervention group (T3), in which a woman was encouraged to invite her husband to a joint counseling session. A woman (and her husband if she chose to invite him) was then counseled on 5 targeted contraceptive methods based on her baseline preferences for family planning (n=200).

Upon the completion of baseline data collection, women were randomized to 1 of the 3 intervention arms or the control arm, such that the intervention assignment was balanced along the following baseline characteristics: the use of family planning, most preferred method attributes, and age. As part of the balancing process, strata by each combination of characteristic values were created, and observations were assigned to their respective strata. Observations within each stratum were then individually randomized to each of the 4 groups by the principal investigator (PI) in a 2:2:2:1 allocation using computer-generated randomization using STATA, version 14 (StataCorp LLC). Following individual randomization, the Innovations for Poverty Action (IPA) Malawi intervention team implemented the intervention in the participants randomized into the intervention arms. Although the implementation team was not involved in the actual randomization process, counselors, who were responsible for administering the correct counseling and follow-up procedures to each respondent, were not blinded to respondent assignments to each of the intervention arms.

### The Intervention

#### Intervention Protocols

All women who consented to participate in the study (T0-T3) were offered a free, private family planning counseling session, which included a risk assessment for contraceptive methods and detailed information on methods switching, side effects associated with each method, and the benefits of contraception and birth spacing. A precounseling survey was administered to each woman, where they were asked to confirm their personal information, including, but not limited to, pregnancy status, current contraceptive use, and preferences for fertility and contraception. During counseling sessions, counselors provided women with information on the range of modern and natural family planning methods based on their respective intervention assignments. Strategies on how to communicate family planning messages with partners and on how to increase partner awareness were conveyed during the sessions. The counseling session lasted no more than 1 hour and was administered in a private room by a counselor who was trained to provide family planning and reproductive health services. To facilitate an effective and open dialog with women during the counseling session, only female counselors were hired. Counselors were hired by IPA Malawi, held a nursing degree, and were trained on the range of counseling protocols over a week. We enlisted the support of the Malawi RHD and several international nongovernmental organizations who work on family planning, including Population Services International (PSI), BLM, the Family Planning Association of Malawi, and FHI360, to help us develop training materials and counseling resources. We also collaborated with the Malawi RHD, BLM, and PSI to assist with counselor training.

#### Counseling for Control Group T0

Following the introductory risk assessment and discussion on the benefits of contraception and birth spacing, women who were assigned to the control arm were counseled on the full range of 13 available family planning methods. Counselors employed the standard-of-care contraceptive method flip chart that is provided by the MOH and RHD and counseled women on each method following the order of methods in the flip chart.

#### Counseling for Intervention Group T1

Before receiving the counseling session, women who were assigned to the intervention arm T1 were encouraged by the counselor to invite their husbands or male partners to participate in a joint family planning counseling session. Following the invitation, women and their husbands (if they chose to invite them) jointly received an introductory risk assessment and discussion on the benefits of contraception and birth spacing. Women and their husbands were then jointly counseled on the full range of 13 available family planning methods using the standard counseling flip chart, as described for intervention arm T0.

#### Counseling for Intervention Group T2

Following the introductory risk assessment and discussion on the benefits of contraception and birth spacing, women who were assigned to the intervention arm T2 were counseled on a targeted number of methods that were chosen based on the respondents’ reported contraceptive preferences at baseline. The objective of this intervention arm was to minimize the choice overload and increase the salience of a woman’s most preferred method attribute (eg, method effectiveness in preventing pregnancy, duration of use, and likelihood of method-related side effects). At baseline, each woman was asked to assign a relative rank to her top 3 most valued method-specific attributes (eg, does she prefer that a method has a lower incidence of side effects over a method that is more effective at preventing pregnancy?). On the basis of her ranking of method attributes, the counselor confirmed the attribute that the woman revealed to be most important (eg, methods with low incidence of side effects) and used a predesigned tailored flip chart (an abbreviated version of the full flip chart) to present a subset of 5 methods that ranked highest along that revealed attribute. Particular emphasis was placed on making the order of presentation salient, in which women were reminded and primed to consider the relative ranking of methods along the stated attribute. Counselors then counseled women on each of the 5 methods following the standard family planning counseling procedure described above. Additional details on each of the predesigned tailored flip charts are presented in Table 2.

**Table 2 table2:** Attribute-method flip chart correspondence.

Flip chart color and methods		Attributes
**Blue**		Effective at preventing pregnancy Duration of effect or lasts long
	Sterilization	
	IUD^a^	
	Implants	
	Injectables	
	Pill	
**Purple**		
	LAM^b^	No risk of harming health
	Two-day method	No effect on monthly bleeding
	Rhythm method	No unpleasant side effects
	Standard days method	Low cost
	Condoms	No risk of infertility
	N/A^c^	Nonhormonal
	N/A	No need to go to the clinic to procure the method
**Pink**		Immediate return to fertility
	Condoms	
	Two-day method	
	Rhythm method	
	Standard days method	
	IUD	
**Yellow**		
	Condoms	Protects against HIV or STId
**Gray**		
	IUD	Want to try something new or tired of old method
	Implants	My doctor recommended it to me
	Sterilization	My husband wanted me to use this method
	Pills	Other women in my family have used this method
	Injectables	Friends have used this method
	N/A	Easily available at clinic
**Orange**		No need to remember to use
	Sterilization	
	IUD	
	Implants	
	Injectables	
**White**		No need to go to the clinic to resupply
	Two-day method	
	Rhythm method	
	Standard days method	
	Sterilization	
	IUD	
	Implants	
**Red**		Concealable
	LAM	
	Two-day method	
	Rhythm method	
	Standard days method	
	Injectables	
**Black**		Does not interfere with sex
	Sterilization	
	IUD	
	LAM	
	Implants	
	Injectables	
	Pills	
**Green**		Control group only
	IUD	
	Implants	
	Sterilization	
	Pills	
	Injectables	
	Condoms	
	LAM	
	Two-day method	
	Rhythm	
	Standard days method	

^a^IUD: intrauterine device.

^b^LAM: lactational amenorrhea method.

^c^N/A: not applicable.

^d^STI: sexually transmitted infection.

#### Counseling for Intervention Group T3

Before receiving the counseling session, women who were assigned to the intervention arm T3 were encouraged by the counselor to invite their husbands or male partners to participate in a joint family planning counseling session. Following the invitation, women and their husbands (if they chose to invite them) received an introductory risk assessment and discussion on the benefits of contraception and birth spacing. In following the counseling protocols of the T2 intervention arm above, a woman and her husband were jointly counseled on a targeted range of 5 family planning methods based on the woman’s highest ranked preferred method attribute she identified at baseline. Before counseling, counselors confirmed the woman’s highest ranked attribute and jointly counseled the woman and her husband on the targeted subset of 5 contraceptive methods that most closely aligned with her most preferred attribute using a tailored, condensed flip chart specified in Table 2.

### Postcounseling Survey

#### Survey Instrument and Rollout

Following the counseling session, counselors conducted a brief survey with all women to assess their experiences with the counseling service. Multimedia Appendix 2 presents the postcounseling survey instrument. A particular aim of this follow-up survey was to elicit women’s preferred choice of contraceptive method and the cited reasons for choosing this method immediately after counseling. Interviews with women and husbands who were present took no more than 15 minutes and were conducted privately in accordance with the standard interviewing procedures that were established for the baseline survey.

#### Postcounseling Package of Services

Following the postcounseling survey, all women (and husbands who participated in the counseling session) were offered the following package of services for a 1-month period:

Transportation service: women (and applicable husbands) were offered a free transportation service from their homes to the Good Health Kauma Clinic for a period of 1 month. The transportation service was provided by a driver who was hired and trained by IPA Malawi. Respondents received the phone number of a female field manager and were instructed to let the field manager contact the driver to transport them to the Good Health Kauma Clinic during the clinic’s normal working hours, that is, from 8 AM to 5 PM from Monday to Saturday. The field manager maintained a daily schedule of respondents who requested the driver’s services, and the respondents were instructed to notify the field manager at least one day before they wish to go to the clinic to ensure that the driver would be able to transport them. The field manager also provided 1 day’s advanced notice to the Good Health Kauma Clinic to inform them of the number of clients who could be expected to attend the clinic on the following day. Each woman who visited the clinic was always accompanied by the female field manager; the presence of another woman in the vehicle acted to minimize potential stigma associated with a woman traveling alone in the company of a man and also provided comfort to the participant.Financial reimbursement for family planning services: finally, women and participating husbands were financially reimbursed for any out-of-pocket expenditures that they incurred for receiving family planning care at the Good Health Kauma Clinic for the 1-month service period. Costs that were eligible for reimbursement included the procurement costs of family planning medications and contraceptive methods, family planning consultation fees, lab test fees, treatment costs for any contraceptive-related side effects and contraindications, expenses associated with switching and discontinuation of methods, and exam fees. Each couple was allowed a maximum reimbursement amount of MWK 17,500 (US $25.00), which could be redeemed by the couple over multiple visits at the Good Health Kauma Clinic. The extent to which a given expenditure at the clinic met the criteria for being reimbursed was determined by the clinician. For every family planning service that was eligible for reimbursement, the cost of the service was deducted from her reimbursement allowance.

In addition, women and participating husbands who experienced any side effects because of contraceptive use over the course of the service period were entitled to free treatment. If a woman or her husband experienced a side effect or contraindication, then she or he may seek care at her nearest public clinic, public hospital, or the Good Health Kauma Clinic. The woman was asked to keep receipts of any costs incurred at the health facility so that she could be reimbursed later. The reimbursement covered the cost of side effects treatment for all family planning methods used by the woman, regardless of where the method or treatment was procured. All reimbursements for incurred costs were distributed as closely as possible to the time that the reimbursable cost was incurred, most likely within 2-3 business days by the field manager.

At the end of the counseling session, the family planning counselor presented a terms of service document, which specified the terms and conditions for each of the abovementioned services to the woman. Multimedia Appendix 2 presents the terms of service documents for each of the 4 interventions. Counselors answered any questions from the woman about the package of services and then asked for the woman’s (and her husband’s) understanding of these terms. Each respondent also received a paper copy of the terms of the service document.

### Follow-up

#### Follow-Up Phased Rollout

Following the 1-month service period, the entire study sample of women was resurveyed with an abbreviated version of the baseline survey questionnaire. Resurveying participants in this manner enables us to create a panel of individual women where each woman is observed at 3 time points. The same protocols regarding data security and confidentiality that were enforced at baseline were implemented once again for each follow-up survey round.

Follow-up surveys were administered in 3 phases: (1) a clinic-based survey that was administered to women (and participating husbands) who visited the Good Health Kauma Clinic, (2) a phone follow-up survey that was administered to women who did not visit the Good Health Kauma Clinic, and (3) an in-person home-based follow-up survey that was administered to women who neither visited the Good Health Kauma Clinic nor were available for a phone follow-up survey.

#### Clinic-Based Survey

The 1-month clinic-based follow-up survey was administered by the local field team and in person to all women (and husbands) who visited the Good Health Kauma Clinic over the 1-month service period. The clinic-based survey, which is an abbreviated version of the main baseline survey instrument, took no more than 20 minutes and was administered by the female field manager who accompanied the woman to the clinic.

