#### Phone Follow-Up Survey

For women who either moved out of Lilongwe or did not visit the Good Health Kauma Clinic, the field team attempted to contact them by phone up to a maximum of 3 times. Women who were reachable by phone were invited to participate in a short phone follow-up survey. To maintain a respondent’s privacy during an attempt to reach her by phone, the field enumerator conducting the call left no indication of the reason for the phone attempt (eg, voicemail, SMS text message) on the respondent’s phone if there was no response to a call. The phone follow-up survey instrument took no more than 20 minutes and was identical to the clinic-based follow-up survey instrument.

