### Follow-Up Surveys

Follow-up surveys began in November, 2 months after the conclusion of the baseline survey. Field activities for the follow-up surveys began with hiring field staff, training, and piloting the follow-up survey instruments in November 2019, which continued through February 2020. During the 4-month follow-up survey period from November 2019 to February 2020, 767 women (including 727 women from the main study and an additional 40 women from the pilot phase of the study, but not including the 15 women who withdrew from the study before the start of the follow-up survey) were reached. Of the 767 women who were reached at the follow-up stage, 731 (95% of women who were eligible for follow-up) successfully completed the follow-up survey. In total, 51 women who were interviewed at baseline are estimated to be lost to follow-up.

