## Discussion

### Principal Findings

The primary objective of this study is to investigate the extent to which user-centered approaches to counseling, by exploiting choice architectural elements around family planning and promoting male involvement, can affect a woman’s immediate stated preferences and realized preferences in a context where her preferences may be sensitive to a range of behavioral biases. Our main outcomes of interest include women’s stated preferred method of contraception, intention to switch to other contraception methods, uptake of their ideal contraceptive method, and realization of their ideal contraceptive preferences. In addition, by observing whether women will seek family planning following their counseling visit, we will examine the short-run stability of their stated preferences and the extent to which these stated preferences are subsequently realized in the face of barriers to use. Data examining the realization of women’s eventual contraceptive preferences (eg, contraceptive uptake, eventual method choice) were collected during clinic visits and at (phone or home) follow-ups across the four arms.

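### When, how and by whom a woman's follow-up is taken depends on whether she attends the clinic after randomisation, and the protocol gives conflicting accounts of when attenders were surveyed

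*Protocol article*

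**What the plan says.** The protocol article gives two accounts of the endline.

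- **After the service month, for everyone.** Follow-Up Phased Rollout states: "Following the 1-month service period, the entire study sample of women was resurveyed with an abbreviated version of the baseline survey questionnaire". The Abstract likewise puts follow-up one month after counseling, and Study Sample and Inclusion Criteria describes a single follow-up survey after the intervention.
- **At the clinic visit, for attenders.** Clinic-Based Survey: the survey was given "in person to all women (and husbands) who visited the Good Health Kauma Clinic over the 1-month service period" and "was administered by the female field manager who accompanied the woman to the clinic". Principal Findings says that data on realized preferences "were collected during clinic visits and at (phone or home) follow-ups across the four arms".

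Non-attenders follow a different route. Under Phone Follow-Up Survey, those who had not attended, or had left the city, were telephoned, with a field enumerator as interviewer ("the field enumerator conducting the call left no indication of the reason for the phone attempt"). Women who could not be reached by phone had one home attempt, also by an enumerator (Home-Based Survey). The questionnaire is the same in all three modes.

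The Home-Based Survey section gives at most three time points per woman: baseline, counseling and follow-up. Attenders therefore have no second, common endline.

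On dates, Intervention Activities has counseling starting in September 2019, while Follow-Up Surveys states: "Follow-up surveys began in November, 2 months after the conclusion of the baseline survey".

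**The concern.** Attendance at the study clinic happens after randomisation and is one route by which counseling could change contraceptive behavior. Primary Outcomes lists the frequency of visits to local clinics, and Principal Findings treats care seeking after counseling as a response to be studied. If attendance decides when, where and by whom the outcome is recorded, the arms can differ in measurement as well as in outcome.

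What is recorded depends on the moment of the interview. An attender interviewed just after receiving a method is counted as a user and has had no time to discontinue. An attender interviewed just before service has none of that visit's uptake recorded. Either way, later changes are not seen, although the reimbursement allowance is one "which could be redeemed by the couple over multiple visits at the Good Health Kauma Clinic" and covers the costs of switching and discontinuation. A non-attender is asked about her status at the end of the service month or later.

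The outcomes exposed are use, switching, discontinuation, adherence and concordance. Analysis Plan addresses attrition and missing data, but mentions neither the date nor the mode of the survey.

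**Working it through.** **Step 1. What attendance determines**

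| | Clinic attender | Non-attender |
|---|---|---|
| Mode | In person, at the clinic | Phone, then home |
| Interviewer | Field manager who travelled with her | Field enumerator |
| Timing, from Clinic-Based Survey and Principal Findings | At the visit, within the service month | After the month, since non-attendance is known only when it ends |
| Timing, from the Abstract and Follow-Up Phased Rollout | After the month | After the month |
| Questionnaire | Same | Same |

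Mode depends on attendance under every section. Timing is where the sections conflict. The visit-day reading is better supported, because the interviewer is identified as the person accompanying the woman to the clinic and accompanied transport was offered only during the service month.

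**Step 2. Dates**

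Counseling began in September 2019 and surveys in November 2019. A woman who attended in September or October cannot have been surveyed at that visit. She was surveyed later, or not in the way described, so timing may vary among attenders too.

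**Step 3. The plan's own power figure**

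Inputs (Sample Size and Power Calculations): 300 v 400 women, 50% v 60%, α = .05.

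- Pooled proportion = (150 + 240)/700 = 0.557
- Null SE = √[0.557 × 0.443 × (1/300 + 1/400)] = 0.0379
- Alternative SE = √(0.25/300 + 0.24/400) = 0.0379
- Two-sided power = Φ[(0.10 − 1.960 × 0.0379)/0.0379] = 75.1% (stated 75%)
- One-sided power = 84.0% (stated 85%)

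The stated power is reproduced to within about a point, and this issue does not alter it.

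**Step 4. Form of the bias**

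Let a₁ and a₀ be the attendance shares in the two groups. Let s be the shift in attenders' recorded outcome, relative to what a common endline would record, taken as equal in both groups. Then

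bias in the contrast ≈ (a₁ − a₀) × s.

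The documents give neither attendance by arm nor s, so the values below are assumptions. Under a true null at 50%, SE = √[0.25 × (1/300 + 1/400)] = 0.0382. The false-positive risk of the planned one-sided test is Φ(bias/0.0382 − 1.645). The last column is one-sided power for a true 10-point effect when the bias runs against the intervention.

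| Attendance difference × shift (assumed) | Bias | One-sided false-positive risk (nominal 5%) | Power (84.0% without bias) |
|---|---|---|---|
| 10 × 10 points | 1 point | 8.3% | 76.6% |
| 10 × 20 or 20 × 10 points | 2 points | 13.1% | 67.7% |
| 20 × 20 points | 4 points | 27.5% | 47.2% |
| 0 × any | 0 | 5% | 84.0% |

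The direction is not known: s is positive if the interview follows service and may be negative if it precedes it.

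**The case against.** The case on the other side has real substance.

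- **Visit-day timing is not established.** The clinic survey is itself called a 1-month follow-up, and its reference to the service period can be read as saying when women visited rather than when they were interviewed. The Abstract, Follow-Up Phased Rollout and the November start all point to later measurement. A reader might infer that every attender's outcome was fixed on the day of her visit; the documents do not support that as fact. What stands is that the sections conflict, and that mode depends on attendance whichever is right.
- **The interviewer split is less sharp than it looks.** Home-Based Survey refers to enumerators explaining each survey, clinic surveys included. Still, Clinic-Based Survey names the accompanying field manager as the person who administered it.
- **Safeguards exist.** The instrument is identical, the service package is offered in all arms, and a private space is required at the clinic. The husband's presence is therefore a weak argument. None of these safeguards equalizes date or setting.
- **A large figure is tempting but wrong.** If 30% attended and 60% of them took up a method at the visit (both assumed), recorded prevalence would move by 0.30 × 0.60 = 18 points depending on whether the interview came before or after service. That is a swing within one arm. It is not a between-arm bias and cannot be set against the 10-point design effect.
- **Discontinuation and adherence are not the powered outcomes.** That is true; the study is powered for uptake and intention to switch. But recorded uptake also depends on whether the interview comes before or after service.
- **The analysis plan is not shown** and may handle survey date and mode. That answers the analysis, but not the contradiction in how the endline is defined.

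**Conclusion.** The point holds in a limited form. Survey mode depends on clinic attendance and, on the better-supported reading, so do timing and interviewer. Attendance is post-randomisation and clinic visiting is a listed primary outcome, so the contrasts for use, switching, discontinuation and concordance can be biased in either direction. The sections on timing contradict one another and must be reconciled.

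The size cannot be derived from the documents. The 1 to 4 points rest on assumed attendance differences and recording shifts of 10 to 20 points each, with the same shift in both groups. If attendance is equal, the bias under the null is zero. Nothing in the documents shows that attendance did differ by arm.

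**What to change.** **Definition.** Reconcile the Abstract, Follow-Up Phased Rollout, Clinic-Based Survey, Follow-Up Surveys and Principal Findings, stating when attenders were in fact surveyed. The sound design is one endline for all women, attenders included, in a single fixed window after the service month, using the phone-then-home sequence and the same instrument, with the clinic interview kept as process data. Its cost is a call of up to 20 minutes per attender by existing enumerators. Fieldwork closed on February 15, 2020, so this can now serve only a later round or a repeat study.

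**Data already collected.**

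- Report days from counseling to survey, and survey mode, by arm.
- Keep all randomised women in the intent-to-treat contrast. Dropping attenders interviewed early would select on attendance.
- Add sensitivity analyses or bounds for clinic-day records, for example by extending the best-worst case approach already planned for missing data. Later visit or reimbursement records belong only in a sensitivity analysis, because they exist mainly for attenders and do not measure ideal method or concordance.
- Do not adjust for mode as an ordinary covariate, since that conditions on a post-randomisation variable.
- Do not claim one-month discontinuation, adherence or sustained concordance from clinic-day interviews.

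The cost is one table by arm, a few added analyses and narrower claims.
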